## Abstract

**Background:**

Cervical radiculopathy is the most common disease in the cervical spine, affecting patients around 50–55 year of age. An operative treatment is common clinical praxis when non-operative treatment fails. The controversy is in the choice of operative treatment, conducting either anterior cervical decompression and fusion or posterior foraminotomy. The study objective is to evaluate short- and long-term outcome of anterior cervical decompression and fusion (ACDF) and posterior foraminotomy (PF)

**Methods:**

A multicenter prospective randomized controlled trial with 1:1 randomization, ACDF vs. PF including 110 patients. The primary aim is to evaluate if PF is non-inferior to ACDF using a non-inferiority design with ACDF as “active control.” The neck disability index (NDI) is the primary outcome measure, and duration of follow-up is 2 years.

**Discussion:**

Due to absence of high level of evidence, the authors believe that a RCT will improve the evidence for using the different surgical treatments for cervical radiculopathy and strengthen current surgical treatment recommendation.

**Trial registration:**

ClinicalTrials.gov NCT04177849. Registered on November 26, 2019

## Administrative information

Note: the numbers in curly brackets in this protocol refer to SPIRIT checklist item numbers. The order of the items has been modified to group similar items (see http://www.equator-network.org/reporting-guidelines/spirit-2013-statement-defining-standard-protocol-items-for-clinical-trials/).

## Introduction

### Background and rationale {6a}

Cervical radiculopathy is a symptom complex consisting of arm pain, impaired sensory and motor function in the corresponding dermatomes and myotomes, and varying degrees of neck pain. The cause is often foraminal stenosis, which is secondary to degenerative disk disease with disk herniation (21.9%) and/or osteophyte formation from the uncovertebral or facet joints (68.4%) compressing the nerve in the root canal [1, 2]. The incidence has been estimated at 83.2 per 100,000 inhabitants/year with a peak at 50–54 years. Men are affected more often than women (107.3 vs. 63.5 per 100,000/year). The most often afflicted nerve root is the C7 root (46.3%), followed by C6 root (17.6%) [2].

The diagnosis is set by the typical history and findings, which often involves loss of sensory and motor function, and diminished deep tendon reflexes. The foraminal compression test is a provocation test for the affected nerve root. The head is extended and rotated towards the affected side. A positive response is when pain is reproduced by axial compression of the head. The clinical results must correlate with the findings of the neuroradiological examination, primarily the MRI but alternatively CT is used in cases where MRI cannot be performed, because of, claustrophobia, non-MRI-compatible pacemaker or dorsal column stimulator, or the presence of other metal objects that may cause damage tissue by shifting position under the exam [3]. In ambiguous cases, neurophysiological examinations may also be valuable.

Spontaneous restitution is common; hence, non-surgical treatment is often the first choice. Non-operative treatment may consist of pain medications, a neck collar, and physiotherapy. Indications for surgery are failure off non-operative therapy, with no relieve if the pain after a period of a couple of months, or if complications occur, i.e., intractable pain, progressive paresis, or cervical myelopathy. In these cases, surgical intervention may result in a reliable improvement and enhanced quality of life [4].

Theoretical advantages of anterior decompression and fusion (ACDF) are the direct removal of the pain-generating disk fragment or osteophyte compression applied to the nerve root. Drawbacks are the approach-related complications, such as injury to neurovascular or other structures, and pseudoarthrosis, which may occur in a number of cases. The most feared acute complication is a postoperative hematoma, which, if untreated, may rapidly lead to airway obstruction or compression of the spinal cord. This occurs with an incidence of 1%. The incidences of other known complications with ACDF are as follows: esophagus lesion 0.25% [5], infection 0.1–1.6% [6], injury to the recurrent laryngeal nerve 0.6–2.9% [7], injury to the superior laryngeal nerve 0–1.25% [8], injury to the hypoglossal nerve 0–1.28% [9], vertebral artery injury 0.08% [10], dural tear 0.5–3.7% [11], spinal cord injury 0–0.24% [12], Horner’s syndrome 0.06% [13], brachial plexus injury 0.1% [14], C5 palsy 0–2.5% [15], and injury to the thoracic duct 0.08% [16].

Other complications associated with the anterior approach include intermittent early dysphagia which in most cases resolves [17]. In addition, adjacent segment disease (ASD) may occur, as spinal fusion has been blamed for increasing the incidence of degeneration in adjacent levels [18]. 25.6% will develop ASD within 10 years after ACDF and 7.5% will need further surgery. However, the cause for ASD is controversial, as disk degeneration is an age-related process affecting all disks and ASD may be a normal progression of the degenerative process affecting the disk adjacent to the fusion [19]. ACDF leads to clinical success in 83–91% of cases, with a reoperation incidence of 4–14% [20, 21].

Theoretical advantages with posterior foraminotomy (PF) include the following: fewer vital structures can be injured during the primary procedure and the segment is left unfused perhaps decreasing the risk for ASD. A disadvantage is that the decompression is indirect, meaning that the compressing fragment or the osteophyte is not removed, but the nerve root is allowed to move away from it, as the “roof” of the foramen is opened.

Approach-related complications with PF are postoperative hematoma, which may compress the spinal cord, and C5 palsy [15], where the exact pathophysiology is not fully understood.

Instability issues after partial facetectomy during PF may lead problems that require fusion, in general fusion after PF have rates of up to 5%. Recent retrospective studies of minimal invasive PF with over 1000 cases shown that a good level of decompression is achieved, i.e., to same or better NDI in comparison to ACDF [22–32].

The incidence of ASD is 6.7% 10 years after one level of PF, with 3.2% requiring reoperation for ASD [33]. The preserved motion may lead to restenosis as the degeneration continues with the risk of secondary surgery on the index level [34]. PF will lead to clinical success in 64–96% with a reoperation incidence of 4–7% in retrospective cohort studies [22–32, 35–37].

Both methods result in a high rate of clinical success with a low incidence of reoperations. However, there are no prospective controlled studies with a high level of evidence comparing the two approaches. High level of evidence from RCTs could improve treatment guidelines and recommendations for the surgical treatment off cervical radiculopathy [38–41].

### Objectives {7}

The main objective of the trial is to compare the clinical outcome of ACDF surgery after 2 years of follow-up with the outcome of PF in patients with cervical radiculopathy by using patient-reported outcome measures (PROMS). The primary outcome variable is the Neck Disability Index (NDI) at the 2-year follow-up [42]. Secondary outcome variables are the European Quality of Life-5 Dimensions (EQ-5D) [43, 44] and the Numeric Rating Scales (NRS) [45] for arm and neck pain. To evaluate temporal differences between the recoveries after each surgical technique, the variables will also be collected after 4 weeks, 3 months, and 1 year. Tertiary variables are complications and secondary surgeries.

### Trial design {8}

The trial is conducted as a multicenter clinical randomized controlled trial (RCT) with 2 years of follow-up using PROMs and radiological parameters. The RCT will be carried out according to the SPIRIT and CONSORT statements for clinical trial reporting [46, 47]. Randomization without stratification in a 1:1 ratio using the SMART-TRIAL software (www.smart-trial.co) will result in allocation to either ACDF or PF, a 2-arm parallel group design. The primary aim is to evaluate if PF is non-inferior to ACDF using a non-inferiority design with ACDF as “active control.” A secondary superiority design will also be applied. In the non-inferiority design, the hypothesis is that PF is equal to ACDF. The difference between PF and ACDF is not more than the MCID for NDI, i.e., not more than 7.5 points or 15% units [48–50].

## Methods: participants, interventions and outcomes

### Study setting {9}

Participating centers are Örebro University Hospital (primary site), Uppsala University Hospital, Umeå University Hospital, and Ryggkirurgiskt Centrum Stockholm. Each center has high volume of cervical radiculopathy patients and complex spine surgery teams to provide the interventions in form of PF and ACDF

### Eligibility criteria {10}

#### Inclusion

The inclusion criteria are as follows: cervical radiculopathy; age 18–65 years; patients with symptoms of radiating arm pain with duration of at least 6 weeks; neck disability index (NDI) over 30 points (60%); correlating findings on MRI, one or two consecutive cervical levels; eligible for both treatments; and ability to understand and read Swedish language.

#### Exclusion

The exclusion criteria are as follows: previous cervical spine surgery; more than two cervical levels requiring treatment; severe facet joint osteoarthritis; symptoms or marked radiologic signs of myelopathy; drug abuse, dementia, or otherwise expected low compliance; cervical deformity or marked instability (3.5-mm translation or > 11 degrees more motion at index level compared to adjacent segments [51]; history of severe cervical trauma, WAD or generalized pain syndrome; pregnancy; rheumatoid arthritis or ankylosing spondylitis; malignancy; active infection or another severe systemic disease; or when the surgeon deems the participant unsuited for either of the interventions.

### Who will take informed consent? {26a}

The consultant spine surgeon will take informed consent during consultation meeting with the patient that is eligible for inclusion.

### Additional consent provisions for collection and use of participant data and biological specimens {26b}

Eligible patients will be informed in the clinic about the study and included if consent is given. Study information is given by the consultant spine surgeon. No other consent provisions are applicable; no biological specimens are collated.

### Interventions

#### Explanation for the choice of comparators {6b}

Treatment for CR in Europe and USA has been ACDF and is considered “Golden standard,” yet in the Asian Pacific, the main treatment for CR is PF. No level one evidence has been published yet; the investigators believe that clinical equipoise is between ACDF and PF.

### Intervention description {11a}

#### Anterior cervical decompression and fusion

A 4-cm anterolateral transverse incision is made over the index level, on either the right or left side according to the surgeon’s preference. Platysma is sectioned transversal to its fibers, and the anterior aspect of the spinal column is bluntly exposed between the carotid sheath and the esophagus. The disk is excised, including the posterior longitudinal ligament. Disk fragments and/or osteophytes from the uncovertebral joint on the affected side are removed until the root is fully decompressed. Reconstruction is typically done with an interbody spacer, autologous bone graft, and a stabilizing plate screwed to the adjacent vertebral bodies. A fusion cage with integrated screws may also be used according to the surgeon’s preference [20, 41].

#### Posterior foraminotomy

A 4-cm longitudinal midline incision exposes the spinous processes of the adjacent vertebrae. The facet joint covering the index foramen is exposed through intermuscular planes. The root canal is opened as the medial third of the facet joint is removed. The affected nerve root is decompressed by laterally undercutting the facet joint throughout its length [36].

#### Criteria for discontinuing or modifying allocated interventions {11b}

If severe adverse events are noted, the attending spine surgeon will contact the investigator of the study. Analysis of severe adverse event will be conducted to evaluate if the method is harmful and then decide to stop the trial. Stopping criteria is difference of over 30% in NDI between the outcomes, i.e., to more than 2x MCID on any of the follow-up PROMS at 4–6 weeks, 3 months, 1 year, and 2 years. Participants can at any time request to drop out of the study.

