### Outcomes {12}

#### Primary variable

The primary outcome, NDI, is a self-administered questionnaire with 10 items measuring disability in patients with neck pain. The questions cover daily activities, such as the ability to dress, lift heavy objects, read, work, drive a car, sleep, and perform leisure time activities, as well as the amount of pain, headache, and concentration abilities. Each item is scored from 0 to 5. The disability is more severe with higher scores, while the maximum score is 50 points. The score is transformed into a percentage score (range 0 to 100%). The minimum clinically important difference (MCID) is considered to be 7.5–8.5 [48, 49] or 17.3% [50]. NDI PROMS are collected pre operation and after 4–6 weeks, 3 months, 1 year, and 2 years.

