### Sample size {14}

The MCID in the NDI is approximately 15% [50], and the standard deviation (SD) in the NDI is 25%. With these parameters, a two-sided superiority trial with significance level at 0.05 and power at 80% will require 44 patients in each group. To make up for crossovers, noncompliance, and follow-up losses, the total number of patients is set at 110.

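### The only numeric stopping criterion is a fixed 30% NDI difference at any visit, whatever the number of completed forms, so a sparse visit could trigger a stop by chance

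*Protocol article*

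**What the plan says.** The protocol article, under Criteria for discontinuing or modifying allocated interventions {11b}, states: "Stopping criteria is difference of over 30% in NDI between the outcomes, i.e., to more than 2x MCID on any of the follow-up PROMS". It then lists the four follow-ups at 4–6 weeks, 3 months, 1 year and 2 years. No confidence interval, test or minimum number of completed forms is attached. The same section gives a second route, a case review of severe adverse events that can also end the trial, without a numeric threshold.

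Interim analyses {21b} plans one look by an independent observer at 40 included patients, covering the NDI difference and adverse effects. The section on the data monitoring committee {21a} counts the 40 as included and operated on. The auditing section {23} says the observer's audit at 40 participants uses data from all four follow-ups. None of these sections adds another NDI boundary.

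The non-inferiority limit, under Trial design {8}, is: "The difference between PF and ACDF is not more than the MCID for NDI, i.e., not more than 7.5 points or 15% units". Sample size {14} gives the spread: "the standard deviation (SD) in the NDI is 25" percent.

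**The concern.** A difference between two observed means can only be judged against its standard error, which depends on the number of forms returned. A fixed cut-off ignores this. Where a visit is well filled, the criterion is very hard to reach. Where a visit is thinly filled, sampling noise alone can reach it.

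The any-visit wording makes the second problem practical. At a look triggered by the 40th patient, the early visits will be nearly complete and the 1-year visit will have barely begun. The criterion gives the 1-year comparison of a handful of patients the same power to end the trial as the 3-month comparison of about thirty. At stake is a randomised comparison, with its primary endpoint at 2 years, being ended on a difference that carries almost no information.

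**Working it through.** **Inputs.** SD 25%, difference 15%, two-sided 0.05, 80% power, 44 per group and 110 in total (Sample size {14}); 1:1 allocation (Trial design {8}); cut-off 30% ({11b}), read as percentage units because it is described as twice the MCID; look at 40 patients ({21b}, {21a}); recruitment from January 20, 2020 to about January 1, 2023 (Trial status).

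**The plan's own figure.** n per group = 2 × 25² × (1.960 + 0.842)² / 15² = 43.6, rounded up to 44. This reproduces the statement that "a two-sided superiority trial with significance level at 0.05 and power at 80% will require 44 patients in each group". The total of 110 is 88 / 0.80. The SD of 25 is therefore a fair basis for the stopping criterion too.

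**Complete data at the look.** With 20 per arm, SE = 25 × √(2/20) = 7.91. An observed 30 is z = 30 / 7.91 = 3.79, two-sided p about 0.00015. The chance of crossing at one visit is P(|observed difference| > 30):

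| True difference | Chance of crossing |
|---|---|
| 0 | 0.015% |
| 15 | 2.9% |
| 20 | 10.3% |
| 22.5 | 17.1% |
| 30 | 50% |

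The criterion applies to any of four visits. If all four were complete for all 40 patients, simulation gives 5.3% to 11.1% at a true 15, for between-visit correlations from 0.9 down to 0 (the correlation is an assumption). With no true difference it gives about 0.04% to 0.06%.

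**Sparse data, no true difference.**

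| Forms per arm | SE = 25 × √(2/n) | 30 / SE | Chance of crossing |
|---|---|---|---|
| 5 | 15.8 | 1.90 | 6% |
| 3 | 20.4 | 1.47 | 14% |
| 2 | 25.0 | 1.20 | 23% |

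**How sparse would the 1-year visit be?** The protocol gives no accrual curve, so assume even accrual and a constant wait for surgery.
- The window is about 35.4 months, so 110 / 35.4 = 3.1 patients a month.
- Forty operations then take 40 / 3.1 = 12.9 months.
- Patients at least 12 months past surgery: 40 − 12 × 3.1 = about 3 in total, both arms together.
- Patients at least 3 months past surgery: 40 − 3 × 3.1 = about 31.
- No patient would have 2-year data.

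Three patients split 2 to 1 give SE = 25 × √(1/2 + 1/1) = 30.6, so 30 / 30.6 = 0.98 and a chance crossing of about 33%.

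The result depends on the counting point. If the 40 are counted at inclusion, as {21b} words it, the 4–18 week wait for surgery pushes the first 1-year forms to about 12.9 months or later. Practically none would then exist at the look.

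**The case against.** The best defence is that an early stopping boundary should be strict. The 15% limit is a margin for the 2-year non-inferiority conclusion; nowhere does the protocol call it a harm that must halt the trial at 40 patients. Low sensitivity at a true 15 is also largely a matter of sample size. With 20 per arm an ordinary two-sided 5% test has only 48% power, and an approximate O'Brien-Fleming-type bound (z about 3.25, an observed difference of about 25.7) would cross about 9% of the time. This stands. The 2.9% shows how strict the criterion is and does not by itself show an error.

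A second defence is that the documents describe one look at 40 patients and do not say the criterion would be used on two or three forms per arm. That is fair. But {11b} names any visit without a minimum, and {23} names the 1-year and 2-year data for the audit at 40, so the text as written permits it. A third is that a condensed article leaves detail to a fuller document, and that adverse-event review offers protection besides the NDI criterion. Both are true, but the article does state a specific criterion, and that criterion takes no account of precision.

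Three stronger readings may tempt a reader and are not supported.
- That twice the MCID conflicts with the rest of the plan. Under Primary variable the text reads "The minimum clinically important difference (MCID) is considered to be 7.5–8.5 [48, 49] or 17.3% [50"%), and 2 × 17.3 = 34.6. But {8} and {14} adopt 15%, and 2 × 15 = 30, so the criterion matches the values the trial uses.
- That the absence of a direction is an error. Both arms are active surgery in declared equipoise, with a secondary superiority aim, and a symmetric criterion is reasonable.
- That a one-sided 95% bound excluding zero is the right replacement. At 20 per arm it fires at an observed 1.645 × 7.91 = 13.0, inside the 15 limit, and in 24% of cases at a true 7.5.

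**Conclusion.** The point holds as a defect of precision. One fixed cut-off is very strict where data are complete and noisy where they are sparse, and the any-visit wording lets the sparse case count. The exposure is a 6% to 23% chance of crossing with 5 to 2 forms per arm and no true difference, against 0.015% at one visit with 20 per arm.

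This rests on the protocol's SD of 25, approximately normal means and, for the count of about 3 patients at 1 year, even accrual and counting the 40 at surgery. Slower early accrual would put more patients past 1 year at the look. Counting at inclusion would leave almost none, and the exposure at that look would largely disappear. The documents do not support saying that the criterion fails to protect patients or that its threshold should be lower. The change is worth making because it is cheap and removes a possible stop by chance.

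**What to change.** Amend {11b} and {21b} together, and align {21a} and {23} with them:
- Apply the NDI criterion only at visits with a prespecified minimum number of completed forms per arm.
- Evaluate it with a confidence interval or a test-based boundary, chosen by the sponsor and stated in advance. No particular boundary is proposed here.
- Make crossing it a prompt for review by the independent observer, who considers it with adverse events and reoperations by arm, not an automatic stop.

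The cost is a paragraph of protocol text, resubmission for ethical approval if the authority treats it as a protocol change, and slightly more analysis at a look that already exists. The downside is that sparse later visits would not count towards the NDI criterion at that look; adverse-event review would still cover those patients.

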#### Strategies to improve adherence to interventions {11c}

Study supervisor will monitor PROMS and radiological parameters; if the participant fails to attend, a written remainder for PROMs, CT scan, and MRI will be sent by mail. This is done on two occasions and with the last and third reminder which is with a phone call. Overall, 3 reminders will be given to the participant before exclusion for non-adherence is conducted.

#### Relevant concomitant care permitted or prohibited during the trial {11d}

Postoperative care, pain control, and physiotherapy will be identical in both groups. The physiotherapy will aim at informing the patient about general mobilization. Neck training will consist of muscular control in the initial phases with range-of-motion exercises starting from 6 weeks postoperatively. Stiff neck collar that affects range of motion is prohibited.

#### Provisions for post-trial care {30}

Patients have in general a standard insurance in case of malpractice and harm provided by the Swedish healthcare system. After the trial has been conducted, the study patients are still eligible for treatment for cervical disorders if needed.

### Outcomes {12}

#### Primary variable

The primary outcome, NDI, is a self-administered questionnaire with 10 items measuring disability in patients with neck pain. The questions cover daily activities, such as the ability to dress, lift heavy objects, read, work, drive a car, sleep, and perform leisure time activities, as well as the amount of pain, headache, and concentration abilities. Each item is scored from 0 to 5. The disability is more severe with higher scores, while the maximum score is 50 points. The score is transformed into a percentage score (range 0 to 100%). The minimum clinically important difference (MCID) is considered to be 7.5–8.5 [48, 49] or 17.3% [50]. NDI PROMS are collected pre operation and after 4–6 weeks, 3 months, 1 year, and 2 years.

